### Study participants

**
*Inclusion criteria*:** 1) Women aged 30–60 years; 2) overweight or obese (waist circumference ≥80 cm)
^
22
^; 3) no prior history of diabetes; 4) not taking any glucose-lowering medications; 5) no prior history of gestational diabetes mellitus (GDM); 6) able to read, write and speak Malayalam, the local language; 7) consents to participate in the trial; and 8) diagnosed with i-IFG (fasting plasma glucose [FPG] 5.6-6.9 mmol/l and 2-hr plasma glucose [2-hr PG] <7.8 mmol/l) on a 2-hr oral glucose tolerance test (OGTT)
^
3
^.

**
*Exclusion criteria*:** 1) Women with known T2DM; 2) having GDM; 3) prior history of GDM; 4) breastfeeding women; 5) having major chronic illnesses including mental disorders, that are likely to impede consenting and participation in the intervention program; 6) taking medications that could alter glucose metabolism (e.g., corticosteroids); and 7) diagnosed with normoglycemia, IGT, and T2DM, as per the American Diabetes Association criteria
^
3
^ on the OGTT.

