### Sample size and randomization

We assumed that the cumulative incidence of regression to normoglycemia at two years would be 18% in the control group (based on unpublished data from the K-DPP trial) and that there would be a 50% relative risk in conversion to normoglycemia with the intervention. The sample size required in each study group was 475 with a type 1 error of 5%, at least 80% power, a contamination rate of 15%, and a 10% loss to follow-up. The sample size required with same estimates and 90% power in each group is 625, and will be recruited, if logistically feasible.

The estimated sample size of 950 participants will be randomly allocated in a 1:1 ratio to the control group and the intervention group using a computer-generated randomization sequence using Microsoft excel by an independent statistician not involved in the trial. The independent statistician will generate the randomized sequence and allocate the individuals to the randomized groups. The participants and the Principal Investigator (EM) will be blinded to the allocation sequence until informed written consent for study participation is obtained. The outcome assessors, data entry personnel and statisticians who analyse the data will be blinded throughout the study as they are not part of the team that delivers intervention or manage the project.

This study uses individual randomization in order to avoid the methodological challenges of cluster randomization, including the clustering effect on statistical power and selection bias, possibility of imbalanced study groups, and the dilution effect
^
23
^. Trial conduct solutions will be put in place to address potential contamination, if any, between the study groups with individual randomization. This include using different staff for each group, education of the participants against contamination
^
23
^, and getting signed nondisclosure agreement from the intervention participants regarding the type of intervention being received. Furthermore, analytical methods that adjust for contamination will also be used. We will also quantify the contamination using a treatment fidelity framework based on the criteria advocated by the Behaviour Change Consortium
^
24
^ and NICE guidance on behaviour change
^
25
^.

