### Recruitment of participants and data collection

Screening and recruitment of participants and data collection will be conducted in 2 stages as described below:

**
*Stage 1: Home visits*.** All women in the age group of 30–60 years will be selected from the voters' list of the selected wards. Eligibility for participation in the study will be ascertained during home visits using a screening questionnaire (includes demographics and eligibility criteria) by trained staff. Only one participant per household (randomly selected) will be screened. Those who meet the eligibility criteria and provide consent for study participation will be screened with a point-of-care glucometer (OneTouch Select Plus, LifeScan Inc.) and their waist circumference will be measured using SECA 201 ergonomic retractable tape with using a standard protocol
^
26
^. Those who are overweight or obese (waist circumference ≥80 cm)
^
22
^ and with a random capillary blood glucose of >110 mg/dl
^
27
^ will be invited to undergo a 2-hr OGTT in clinics organized in their neighbourhoods. These individuals will be considered to be at high risk for having prediabetes or diabetes.

**
*Stage 2: Clinics*.** The high-risk individuals will attend clinics organized in their neighbourhoods, where they will undergo a 2-hr OGTT, body composition, anthropometric, and blood pressure measurements, and interviews to complete the questionnaires. Those diagnosed with T2DM on the OGTT will be referred to the nearby health facility for treatment and care. Body fat composition will be assessed using TANITA DC 360 (pole). Blood pressure will be measured using an OMRON HEM-7120 blood pressure monitor using the standard protocol
^
26
^.

The weight and height will be measured using SECA 813 flat scale and SECA 213 stadiometer, respectively, with a standard protocol
^
26
^. Blood samples will be collected in a fasting state (8–10 hours of fasting) and will be centrifuged within 30 mins after collection and transported to a lab accredited by the National Accreditation Board for Testing and Calibration Laboratories (NABL)
^
28
^. Questionnaires will be administered by trained staff to collect information on demographics, diet
^
29
^, physical activity
^
26
^, tobacco use
^
26
^, alcohol use
^
26
^, diabetes knowledge
^
30
^, prediabetes knowledge
^
31
^, health-related quality of life (HRQoL)
^
32
^; self-efficacy for managing chronic diseases
^
33
^, risk perception for diabetes
^
34
^, social support
^
35

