^, and sleep hygiene
^
36
^ using standardized questionnaires (
Table 1). Those who are diagnosed with diabetes at 12
^th^ and 24
^th^ month assessment will be referred to the nearby health facility for treatment and care, and will continue to participate in the trial. All assessments done at the baseline will be repeated at 12 months and 24 months.

**Table 1. T1:** Outcomes, measurement tools, and data collection time points.

Outcome measures	Variable	Tools/tests used	Baseline	Regular assessment	12 months	24 months
Primary outcome for effectiveness						
Regression of i-IFG to normoglycemia at 12 and 24 months	Fasting plasma glucose and 2-hr post-load plasma glucose	OGTT in a NABL accredited laboratory ^ 28 ^	✓		✓	✓
Secondary outcomes for effectiveness						
Incidence of diabetes	Fasting plasma glucose, 30 minutes and 2-hr post- load plasma glucose, HbA1c	NABL accredited laboratory ^ 28 ^	✓		✓	✓
Insulin sensitivity	Fasting insulin, 2-h insulin, Homa IR	NABL accredited laboratory ^ 28 ^	✓		✓	✓
Beta cell function	Fasting insulin, 2hr insulin, Homa B		✓		✓	✓
Lipid profile	Total cholesterol, triglycerides, HDL-cholesterol, and LDL-cholesterol	NABL accredited laboratory ^ 28 ^	✓		✓	✓
Liver function tests	Aspartate aminotransferase (AST), alanine aminotransferase (ALT), gamma-glutamyl transferase (GGT)	NABL accredited laboratory ^ 28 ^	✓		✓	✓
Blood Pressure	Systolic and diastolic blood pressure	OMRON electronic blood pressure monitor	✓		✓	✓
Anthropometrics	a. Weight b. Height c. Waist circumference	a. SECA weighing scale b. SECA stadiometer c. SECA non-elastic tape	✓		✓	✓
Body composition measures	a. Fat percent b. Muscle mass	TANITA body fat analyser	✓		✓	✓
Psychosocial variables	a. Diabetes knowledge b. Knowledge on prediabetes c. Health-related quality of life d. Self-efficacy/self-empowerment e. Risk-perception for diabetes f. Social support g. Sleep Hygiene	a. 24 Item Diabetes Knowledge Questionnaire ^ 30 ^ b. Prediabetes Knowledge Questionnaire ^ 31 ^ c. WHO QoL BREF scale ^ 32 ^ d. Health Lifestyle and Personal Control Questionnaire ^ 33 ^ e. Scale by Hivert *et al.* ^ 34 ^ f. Scale by Sarason *et al.* ^ 35 ^ g. Sleep Hygiene Index scale by Mastin *et al.* ^ 36 ^	✓		✓	✓
Behavioural outcomes for effectiveness and implementation						

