### Outcomes

The primary outcome for the effectiveness study will be normoglycemia, defined as FPG<5.6 mmol/l and 2-hr PG<7.6 mmol/l, at 24 months
^
3
^. Secondary outcomes will include incidence of T2DM (fasting plasma glucose ≥ 7.0 mmol/l or 2hr PG ≥ 11.1 mmol/l or HbA1c ≥6.5%), insulin sensitivity, beta cell function, weight, body mass index, waist circumference, FPG, 2-hr PG, blood pressure, body composition measures (fat percent and muscle mass) and psychosocial variables (health-related quality of life, self-efficacy/self-empowerment, risk-perception for diabetes, social support and sleep hygiene). Implementation outcomes include reach, effectiveness, adoption, implementation and maintenance of the intervention
^
16
^.

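### Incident T2DM can be met by HbA1c alone, but entry screens for undiagnosed diabetes by OGTT only, so some women already meet the outcome at baseline

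*Protocol article*

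**What the plan says.** Entry (Study participants). The glycaemic inclusion criterion is "diagnosed with i-IFG (fasting plasma glucose [FPG] 5.6-6.9 mmol/l and 2-hr plasma glucose [2-hr PG] <7.8 mmol/l") on an OGTT. Diagnosed diabetes is kept out by history: no prior diabetes, no glucose-lowering medication, and the exclusion "Women with known T2DM". Undiagnosed diabetes is covered by the exclusion of women "diagnosed with normoglycemia, IGT, and T2DM, as per the American Diabetes Association criteria", and that sentence goes on to tie the diagnosis to the OGTT. None of these criteria mentions HbA1c.

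Screening clinic (Recruitment of participants and data collection, Stage 2). "Those diagnosed with T2DM on the OGTT will be referred to the nearby health facility for treatment and care". The follow-up counterpart in the same section refers women found to have diabetes at 12 or 24 months and keeps them in the trial, without limiting the diagnosis to the OGTT.

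Outcome (Outcomes). The secondary outcome is "incidence of T2DM (fasting plasma glucose ≥ 7.0 mmol/l or 2hr PG ≥ 11.1 mmol/l or HbA1c ≥6.5"%). Any one of the three routes is sufficient, and nothing is said about the baseline value.

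Measurement (Table 1). The row for incidence of diabetes lists "Fasting plasma glucose, 30 minutes and 2-hr post- load plasma glucose, HbA1c", ticked at baseline, 12 and 24 months. The text adds: "All assessments done at the baseline will be repeated at 12 months and 24 months".

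Analysis (Data analysis). Categorical secondary outcomes get log-binomial models under the intention-to-treat principle. No at-risk set is given for incident T2DM.

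**The concern.** An incidence outcome needs a population that is free of the condition at the start, judged by the same definition that is applied later. Here the laboratory definition has two routes at entry (fasting and 2-hour glucose) and three at follow-up (those two plus HbA1c). A woman can be positive by the third route on the day she is randomised, and nothing in the stated rules removes her from the count.

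If such women are counted, the outcome mixes new diabetes with diabetes that was already present by the trial's own definition. Absolute incidence is too high in both arms. The relative risk is diluted if these women's status does not respond to the programme. If it does respond, the outcome credits reversal of existing disease as prevention. In either case it does not measure what its name says. The Introduction sets the trial against earlier i-IFG subgroup results on diabetes incidence, so readers are likely to compare this outcome with them.

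**Working it through.** **Step 1: the rules side by side.**

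| Route to diabetes | Laboratory exclusion at entry | Incident T2DM at 12 and 24 months |
|---|---|---|
| Fasting glucose ≥7.0 mmol/l | yes (OGTT; entry range 5.6-6.9) | yes |
| 2-hour glucose ≥11.1 mmol/l | yes (OGTT; entry limit below 7.8) | yes |
| HbA1c ≥6.5% | no | yes |

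**Step 2: a hypothetical case.** An undiagnosed woman has fasting glucose 6.2 mmol/l, 2-hour glucose 7.0 mmol/l and HbA1c 6.6%. She meets every glycaemic entry criterion. With identical values at 12 months she satisfies the outcome definition through HbA1c, although nothing has changed.

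**Step 3: what is not affected.** The article gives no planning figure for incident T2DM. Its sample size rests on the primary outcome, where "the cumulative incidence of regression to normoglycemia at two years would be 18% in the control group". Reading the stated effect as 18% against 27%, with two-sided 5% error, 80% power and a continuity correction, gives 359 per group. Then 359 / 0.85 / 0.90 = 469, close to the stated 475. HbA1c enters neither this calculation nor the primary outcome, which uses fasting and 2-hour glucose.

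**Step 4: illustrative size.** Inputs:
- I, two-year incidence of new T2DM in controls. The Introduction gives 5-10% a year for prediabetes overall, so 1 − 0.95² = 0.0975 and 1 − 0.90² = 0.19; taken as 0.10 to 0.19. This is not an i-IFG figure.
- p, share of enrolled women with baseline HbA1c ≥6.5%: assumed 0.01 to 0.05. Of 950 women that is 9.5 to 47.5, about 10 to 48.
- s, share of those women still ≥6.5% at follow-up: assumed 0.5 to 1.0.
- True RR for new T2DM: assumed 0.70.
- k, ratio of persistence in the intervention arm to that in the control arm: 1 if the programme has no effect on these women.

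Control rate as counted: C = I(1 − p) + ps.

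Intervention rate as counted: T = 0.70·I(1 − p) + k·ps.

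Observed RR = T/C. Share of counted control cases that were present at baseline = ps/C.

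With k = 1:

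| p | s | I | C | T | Observed RR | Share |
|---|---|---|---|---|---|---|
| 0.01 | 0.5 | 0.19 | 0.1881 + 0.005 = 0.1931 | 0.1317 + 0.005 = 0.1367 | 0.708 | 3% |
| 0.01 | 1.0 | 0.19 | 0.1881 + 0.010 = 0.1981 | 0.1317 + 0.010 = 0.1417 | 0.715 | 5% |
| 0.05 | 0.5 | 0.10 | 0.0950 + 0.025 = 0.1200 | 0.0665 + 0.025 = 0.0915 | 0.763 | 21% |
| 0.05 | 1.0 | 0.10 | 0.0950 + 0.050 = 0.1450 | 0.0665 + 0.050 = 0.1165 | 0.803 | 34% |

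The observed RR therefore lies between about 0.71 and 0.80. Counted control incidence rises from 19% to 19.3% at the mild end and from 10% to 14.5% at the severe end.

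**Step 5: if the programme does act on these women.** With k = 0.70 the observed RR stays at 0.70 for any p and s. With k = 0.5 in the last row, T = 0.0665 + 0.025 = 0.0915, and 0.0915 / 0.1450 = 0.63, which is below the true RR for new disease. The direction of the distortion thus depends on k.

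**The case against.** The strongest reply is that the article never says that baseline-positive women will be counted as new cases. Incidence ordinarily implies absence at baseline, HbA1c is scheduled at baseline in the very row for this outcome, and an analysis plan not shown could restrict the at-risk set. That stands in part: the counting is an inference from the definition, not an explicit statement. But eligibility and outcome definition are protocol content. Both are spelled out here, they differ, and followed literally they give the wrong count. This is more than a detail left for later.

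Other limits stand in full:
- A reader might infer that diabetes is ruled out by OGTT alone. The documents do not support that, because history and medication also exclude. Only undiagnosed women with qualifying glucose values and a raised HbA1c are affected, and their number is unknown.
- A reader might take incident T2DM to be the main secondary outcome. It is listed first, but the article does not rank the secondary outcomes.
- A reader might take an RR of 0.80, or a 34% share of cases, as the expected distortion. Those are upper-end results under full persistence, no programme effect and the highest assumed prevalence.
- A reader might infer that the bias must run toward 1. Randomisation balances these women in expectation, and dilution follows if the programme leaves their HbA1c unchanged. A 12-month diet and weight-loss programme could lower it.

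The referral wording alone is weak evidence, since screening and follow-up serve different purposes. It is relevant only because the word diabetes appears to cover different tests at the two times.

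**Conclusion.** The mismatch is real and sits in the current text. Laboratory exclusion of undiagnosed T2DM at entry uses the OGTT, while the secondary outcome can be met by HbA1c alone, with no condition on the baseline HbA1c that the trial already measures. Applied as written, the definition counts unchanged women as incident cases.

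The size cannot be fixed from the documents, because they give no baseline HbA1c distribution. Under the assumptions in the working, with no programme effect on the affected women, a true RR of 0.70 would be seen as about 0.71 to 0.80. If the programme lowers their HbA1c, dilution shrinks or reverses.

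The conclusion does not extend to the primary outcome, the sample size, or any claim that women with known diabetes are enrolled. The point should be corrected, but it does not threaten the trial's main result.

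**What to change.** Add one sentence to the Outcomes or Data analysis section: the at-risk set for incident T2DM is randomised women with baseline HbA1c below 6.5%. Report by arm the number at or above 6.5%, and keep all randomised women in the primary analysis. The restriction uses a baseline measurement unaffected by the programme, so the randomised comparison is preserved.

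An alternative that also removes the mismatch is to define incident T2DM by the OGTT and show the definition with HbA1c as a sensitivity analysis. That gives up HbA1c as a route in the main analysis of this outcome.

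The sponsor should also reconcile the entry criteria, the screening and follow-up referral wording, and the outcome definition, so that it is clear which tests establish diabetes at each time point. Which clinical rule applies is for the sponsor to decide.

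Cost: no new data, and a slightly smaller denominator for this one outcome (about 10 to 48 fewer of 950 women on the assumed 1-5%). The trial is reported as still screening, so the change can be made before outcome data exist.

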### Study groups

**
*Control group*.** Participants in the control group will receive a health information leaflet at baseline in local language (
*Malayalam)* on strategies for diabetes prevention. No further engagement will be there in the control group apart from follow-up assessments at 12 and 24 months.

**
*Intervention group*.** The study participants in the intervention group will receive an intensive lifestyle modification program for a period of 12 months through group and individually mentored sessions. The intervention will include behavioural determinants such as self-efficacy, risk perception, social support, and behavioural change techniques, including knowledge enhancement, self-monitoring, goal setting and review, and peer support
^
38
^ (
Table 2). The intervention will be intense as the engagement is not just limited to group sessions, but also involves individualized support through peer mentors and individualized instructions through a mobile application, specifically made for this trial.

**Table 2. T2:** Program goals, theory-based methods, and strategies (Adapted from the Kerala Diabetes Prevention Program) [Source: Elezebeth et al. Cultural adaptation of a peer-led lifestyle intervention program for diabetes prevention in India: the Kerala Diabetes Prevention Program (K-DPP)
^
38
^]

Program Goals	Personal learning and Social environmental change objectives	Determinants based on theory and evidence	Behaviour change techniques	Feasible and culturally acceptable strategies to enhance engagement and implementation
a. Weight loss by 5–7% ^ 6 ^ b. Reduction in waist circumference by ≥4 cm ^22^ c. Reduction in body mass index ^ 6 ^ by ≥0.5 kg/m ^2^ d. Increased consumption of fruit and vegetables (>5 servings/day) ^ 39 ^ e. Increased physical activity through walking, exercise, and culturally appropriate activities (>150 minutes/ week) ^ 40 ^ f. Improved sleep hygiene ^ 41 ^	**Personal learning objectives** • Increase in awareness of risk factors of T2DM • Improve risk perception on T2DM • Improve self-efficacy in making lifestyle changes **Social Environment change** **objectives** • Enhance peer support for behaviour change • Enhance household/family support for behaviour change • Facilitate opportunities for healthy lifestyle in collaboration with group members • Empowerment for diabetes prevention	• Risk perception • Self-efficacy • Social support • Availability and accessibility of facilities for physical activity and healthy food options	• Provide information on the risk factors of T2DM • Provide information on the dietary and physical activity targets for individuals. • Self-monitoring • Goal setting and goal review with emphasis on participants and family member outcomes • Peer support • Social and practical support from family, neighbourhood members and community organizations (Panchayats) • Engage and empower family and group members to increase availability and accessibility of healthy food options and physical activity options	**Individual-level** • Educational sessions that focus on ‘modifiable’ determinants of risk on diabetes. • Sessions scheduled in local neighbourhoods (e.g. a reading room or *Kudumbashree’s meeting* *rooms*) according to work, family and other cultural needs of participants **Interpersonal-level (family)** • Group-based delivery • Inclusion of family members in the sessions • Enabling ongoing peer and social support, with family members and friends of participants • Kitchen garden training to facilitate vegetable consumption and increase enjoyable physical activity • Forming walking groups or other activity groups such as yoga or aerobic dance groups as appropriate.

**
*Theory of intervention*.** The intervention program objectives, theory-based methods, and strategies for intervention engagement and implementation are given in
Table 3. Briefly, the intervention was adapted from a successfully conducted lifestyle-based diabetes prevention trial in Kerala, the K-DPP
^
38
^ Program objectives will be achieved through “personal learning” and “environmental change” using evidence-based behaviour change techniques with strategies targeting participants at individual, interpersonal and community levels.

**Table 3. T3:** Intervention sessions schedule.

Session	Individual/ Group	Theme	Activity (AV aid)	Duration	Facilitator
1	G	1.1 Introduce the project 1.2 Rapport building 1.3 Knowledge enhancement	1.1.1 Introduction about the project, requirements and commitments 1.2.1 Building rapport with the participants 1.2.2 Identification of peer mentor 1.3.1 Discuss about diabetes and prediabetes (IFG & IGT) (Flipchart & Mobile based application) 1.3.2 Discuss about risk factors of diabetes (Flipchart & Mobile based application)	20 Min 15 Min 30 Min 20 Min 20 Min	Research Team
2	G	2.1 Risk factor Modification- Unhealthy break/>diet 2.2 Self-monitoring of dietary intake 2.3 Knowledge enhancement on dietary allowances and recommendation for fat/sugar/ vegetables/fruits/salt/rice) 2.4 Goal setting 2.5 Diet monitoring	2.2.1 Self-monitoring work sheet (Flipchart & participant workbook) 2.3.1 Education on healthy diet practices [session+ activity] (Flip chart & Mobile based application) 2.4.1 Individualised goal setting (Flipchart & participant workbook) 2.5.1 Personalized diet planning tool using an interactive mobile application platform.	20 Min 20 Min 20 Min 15 Min	Research Team
3	I	3.1. Diet goal monitoring and revisiting the goals	3.1.1. Goal monitoring (participant workbook) 3.1.2. Identification of barriers 3.1.3. Goal resetting (if needed)	10 Min 10 Min 10 Min	Peer mentor
4	G	4.1 Demonstration of healthy diet option (Salad preparation) 4.2 Physical activity promotion 4.3 Self-monitoring 4.4 Knowledge enhancement on strategies to improve PA 4.5 Goal Setting	4.1.1 Demonstrate the preparation of healthy diet (salad) 4.2.1 Discuss on physical activity and its importance (Flip chart) 4.3.1 PA self-monitoring worksheet (participant workbook) 4.4.1 Discuss on the types of physical activities that are culturally appropriate and feasible (Flipchart & participant workbook) 4.5.1 Individualised goal setting (Participant workbook)	20 Min 15 Min 15 Min 25 Min 15 Min per participant	Research Team
5	I	5.1 PA goal monitoring and revisiting the goals 5.2 Diet goal monitoring and revisiting the goals	5.1.1 Goal monitoring (Participant workbook) 5.1.2 Identification of barriers 5.1.3 Goal resetting (if needed) 5.2.1 Goal monitoring (Participant workbook) 5.2.2 Identification of barriers 5.2.3 Goal resetting (if needed)	30 Min per participant	Peer mentor
6	1	6.1 PA goal monitoring and revisiting the goals 6.2 Diet goal monitoring and revisiting the goals	6.1.1 Goal monitoring (Participant workbook) 6.1.2 Identification of barriers 6.1.3 Goal resetting (if needed) 6.2.1 Goal monitoring (Participant workbook) 6.2.2 Identification of barriers 6.2.3 Goal resetting (if needed)	30 Min per participant	Peer mentor
7	G	7.1 Knowledge enhancement - Effect of stress on diabetes and other chronic diseases 7.2 Strategies for Stress Management 7.3 Strategies to enhance Sleep hygiene	7.1.1 Awareness on impact of stress and importance of managing it (Flipchart & m health app) 7.2.1 Identification of Stress factors (Flipchart) 7.2.2 Demonstration of various stress management techniques (Breathing exercise and yoga) 7.3.1 Educate about the importance of maintaining sleep hygiene (Flipchart)	20 Min 20 Min 10 Min 15 Min	Research Team
8	I	8.1 PA goal monitoring and revisiting the goals 8.2 Diet goal monitoring and revisiting the goals	8.1.1 Goal monitoring (Participant workbook) 8.1.2 Identification of barriers 8.1.3 Goal resetting (if needed) 8.2.1 Goal monitoring (Participant workbook) 8.2.2 Identification of barriers 8.2.3 Goal resetting (if needed)	30 Min per participant	Peer mentor
9	I	9.1 PA goal monitoring and revisiting the goals 9.2 Diet goal monitoring and revisiting the goals	9.1.1 Goal monitoring (Participant workbook) 9.1.2 Identification of barriers 9.1.3 Goal resetting (if needed) 9.2.1 Goal monitoring (Participant workbook) 9.2.2 Identification of barriers 9.2.3 Goal resetting (if needed)	30 Min per participant	Peer mentor
10	G	10.1 Tobacco and alcohol cessation	10.1.1 Create awareness on impact of alcohol and tobacco in the development of T2DM 10.1.2 Refer the participants who use tobacco and alcohol to cessation clinics (if needed)	20 Min	Research Team
11	I	11.1 PA goal monitoring and revisiting the goals 11.2 Diet goal monitoring and revisiting the goals	11.1.1 Goal monitoring (Participant workbook) 11.1.2 Identification of barriers 11.1.3 Goal resetting (if needed) 11.2.1 Goal monitoring (Participant workbook) 11.2.2 Identification of barriers 11.2.3 Goal resetting (if needed)	30 Min per participant	Peer mentor
12	I	12.1 PA goal monitoring and revisiting the goals 12.2 Diet goal monitoring and revisiting the goals	12.1.1 Goal monitoring (Participant workbook) 12.1.2 Identification of barriers 12.1.3 Goal resetting (if needed) 12.2.1 Goal monitoring (Participant workbook) 12.2.2 Identification of barriers 12.2.3 Goal resetting (if needed)	30 Min per participant	Peer mentor

